**Methods/design:**

The study design is a randomized controlled trial. Patients with nonspecific chronic low back pain of more than three months duration are recruited at Rehabilitation Center of Taboao da Serra - SP (Brazil). After examination, sixty-six patients will be randomized into one of two groups: acupuncture group (AG) (n = 33) and electroacupuncture group (EG) (n = 33). Interventions will last one hour, and will happen twice a week for 6 weeks. The primary clinical outcomes will be pain intensity as measured and functional disability. Secondary outcomes: quality of pain, quality of life. perception of the overall effect, depressive state, flexibility and kinesiophobia. All the outcomes will be assessed will be assessed at baseline, at treatment end, and three months after treatment end. Significance level will be determined at the 5 % level. Results of this trial will help clarify the value of acupuncture and electroacupuncture as a treatment for chronic low back pain and if they are different.

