## Methods and design

This study will be a randomized controlled trial, approved by the Ethics Committee of the School of Medicine of the University of Sao Paulo (protocol study 350/13), and funded by the Coordenação de Aperfeiçoamento de Pessoal de Nível Superior (CAPES). To examine the longevity of any intervention effects, measurements will be taken before treatment, after 6 weeks of treatment and 3 months after the intervention. This randomized controlled clinical trial began recruitment on January 16, 2014 and the anticipated completion date is April 2015. We will recruit 66 patients at the Rehabilitation Center of Taboao da Serra, Sao Paulo, Brazil.

After submitting informed consent and being randomized, patients will receive 12 sessions of Chinese acupuncture (acupuncture group (AG)) and EA treatment (EA group (EG)) lasting one hour, twice a week for 6 weeks. Patients will be asked to accept assessments at baseline and at the end of the first and second weeks of the treatment phase. The protocol for the AG is described in Table 1.

**Table 1 Tab1:** Protocol for acupoints used in the project

Acupoints	Location	Major indication e Function
BV 41(Zulinqi)	On the dorsum of the foot, the proximal angle between the fourth and fifth metatarsal bone on the lateral depression of the extensor tendon of the little finger	Relieves joint stiffness and muscle spasms
TA 5 (Waiguan)	Near the dorsal wrist crease between the radius bone and ulna	Relaxes and strengthens tendons
E 36 (Zusanli)	Three inches below the patella between the anterior tibia and the extensor digit rum longs muscle	Tiredness, fatigue caused by weakness and irritability
H 3 (Shaohai)	With the elbow flexed, between the inner end of the cubital crease and the epicondyle of the humerus	Soothes and strengthens the mind
LI 4 (Hegu)	The dorsal side of the hand between the first and second metacarpal bone of the middle dorsal interosseous muscle, opening the thumb and forefinger in the middle of the junction line between the first and the second metacarpal bone	Spasm in fingers
R7 (Fuliu)	Two inches above the point R3 on the anterior medial edge of the soleus muscle	Leg muscle atrophy; swelling
GV 4 (Mingmen)	The dorsal midline in the depression below the spinous process of vertebra L2	Strengthens the lower back and knees
BP 6 (Sanyinjiao)	Three inches above the medial malleolus in the posteromedial border of the tibia	Pain, weakness and imbalance; motor and mental asthenia

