#### Sample size calculation

Sample size was defined in order to detect a 2-point difference between groups on the pain intensity outcome measured by the Pain Numerical Rating Scale, assuming a standard deviation of 1.9 points [23]. We also sought power to detect a 4-point difference in functional disability measured by the Roland Morris Disability Questionnaire, with an estimated standard deviation of 4.9 points [24, 25]. Power was defined as 80% for an alpha of 5% and attrition (drop-outs) of 15%. Accordingly, 33 participants per group will be needed.

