#### Statistical analysis

Data normality will be tested through visual inspection of histograms. The statistical analysis of our study will follow intention-to-treat principles. Repeated measures analysis of variance (ANOVA) will be used to investigate the effect of treatment (Acupuncture vs Electroacupuncture), time (baseline, post-treatment, 3 months follow up), and interaction terms between treatment group versus time. If differences between groups were identified, the Turkey-test for multiple comparison will be conducted. Two-sided paired t tests will use for within-group comparisons (comparing baseline to follow up). If we found non-normally distributed data, we will use the Kurtosis-Wallis test. For all of these analyses, we will use the SPSS version 21 software (SPSS Inc, Chicago, Illinois).The confidence interval will be established at 95%, and the significance level at 0.05.

The relative gain (RG) with treatment will be calculated with the following equation:$$ R{G}_i=\frac{\left( Baselin{e}_i-En{d}_i\right)\times 100}{Baselin{e}_i} $$

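### The repeated-measures ANOVA treats baseline as one of three outcome levels, which cuts the treatment term by a third and can leave disability below the stated 80% power

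*Protocol article*

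**What the plan says.** Under Methods and design, the article states that "measurements will be taken before treatment, after 6 weeks of treatment and 3 months after the intervention". The Statistical analysis section then specifies a repeated-measures ANOVA to examine the "effect of treatment (Acupuncture vs Electroacupuncture), time (baseline, post-treatment, 3 months follow up), and interaction terms between treatment group versus time". The pre-treatment score is thus one of the three levels of the time factor. Baseline adjustment is not mentioned. Post-hoc testing follows if group differences are found, but the section does not say whether the main effect or the interaction establishes them.

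The Sample size calculation section uses plain between-group differences: a "2-point difference between groups on the pain intensity outcome measured by the Pain Numerical Rating Scale, assuming a standard deviation of 1.9 points", and a "4-point difference in functional disability measured by the Roland Morris Disability Questionnaire, with an estimated standard deviation of 4.9 points". It adds that "Power was defined as 80% for an alpha of 5% and attrition (drop-outs) of 15" per cent, and concludes that "33 participants per group will be needed". It gives no correlation between visits and makes no allowance for averaging over baseline.

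**The concern.** A visit before treatment carries no information about the treatment effect except through its correlation with later scores. Entered as an outcome level, it pulls the treatment main effect towards zero and passes part of any chance baseline difference into the estimate.

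The interaction term removes the baseline difference, but in the manner of a change score. It subtracts baseline in full rather than in proportion to its correlation with follow-up, and it spreads the comparison over 2 degrees of freedom. It gives no single between-arm estimate.

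Neither term is the comparison on which the trial was sized. Disability is one of the two primary outcomes, and the Discussion says the open question is whether one technique is better than the other. A real 4-point Roland Morris difference could be missed and read as equivalence of the techniques.

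**Working it through.** **Inputs from the article.** Roland Morris: difference 4, SD 4.9. NRS: difference 2, SD 1.9. Alpha 5%, power 80%, loss 15%, and "acupuncture group (AG) (n = 33) and electroacupuncture group (EG) (n = 33"). Two-sided testing is stated only for the within-group comparisons ("Two-sided paired t tests will use for within-group comparisons") and is assumed between groups.

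**Assumptions.** 28 analysed per arm (33 × 0.85 = 28.05), equal variance s² at each visit, a common between-visit correlation r (not in the article, so a range is shown), and the full difference d at both follow-ups unless stated otherwise.

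**The plan's own figure.** For Roland Morris, n = 2(1.96 + 0.84)² × 4.9²/4² = 23.6, so 24 per arm, and 24/0.85 gives 29. A t-based calculation gives 25, then 30. For NRS it is 15, then 18. The stated 33 is slightly above these and errs on the safe side. A plain t test at one visit with 28 per arm has noncentrality 4/(4.9√(2/28)) = 3.05 and 85% power for Roland Morris. For NRS it has 97%.

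**Treatment main effect.** This is a two-sample t test on each patient's mean over three visits. The expected difference is (0 + 4 + 4)/3 = 2.67, and the SD is 4.9√((1 + 2r)/3). At r = 0.5 the SD is 4.00, the noncentrality is 2.67/(4.00√(2/28)) = 2.49 on 54 df, and power is 69%.

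**Interaction.** Noncentral F on (2, 108) df with λ = (28/2)(2 × 4²/3)/(4.9²(1 − r)) = 6.22/(1 − r). At r = 0.3, λ = 8.89 and power is 75%.

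**Baseline as covariate.** The residual SD is 4.9√(1 − r²) at one follow-up and 4.9√((1 + r)/2 − r²) for the mean of the two.

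Power for Roland Morris, 28 per arm:

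| Test | r = 0.2 | r = 0.3 | r = 0.5 | r = 0.7 |
|---|---|---|---|---|
| Treatment main effect, three levels | 83% | 78% | 69% | 61% |
| Group-by-time interaction | 69% | 75% | 89% | 99% |
| ANCOVA, one follow-up | 86% | 88% | 93% | 99% |
| ANCOVA, mean of two follow-ups | 98% | 98% | 99% | 99.9% |

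The main effect reaches 80% only for r up to 0.26, and the interaction only for r of at least 0.37. A simulation of 6,000 trials at r = 0.5 gave 68.9%, 89.2%, 92.8% and 99.0% for the four rows, in agreement with the formulas. At r = 0.5 the main effect would need 37 analysed per arm, and 37/0.85 gives 44 randomised.

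**Other cases.**
- All 33 per arm retained: main effect 85%, 76% and 68% at r = 0.3, 0.5 and 0.7.
- Effect at 6 weeks only, 28 per arm: the contrast falls to 4/3, and main-effect power is 28% to 20% for r = 0.3 to 0.7.
- NRS main effect, 28 per arm: 94%, 89% and 82% at r = 0.3, 0.5 and 0.7, and 79% at r = 0.8.

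**Chance imbalance.** The NRS baseline difference has standard error 1.9√(2/33) = 0.468, so an imbalance above 0.5 point has probability about 29%. Given an imbalance of 0.5 and r = 0.5, each follow-up difference is expected to shift by 0.25. The main effect then shifts by (0.5 + 0.25 + 0.25)/3 = 0.33, and a change score by 0.25 − 0.5 = −0.25. Adjustment for baseline removes the shift.

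**The case against.** The best defence is that the article lists the usual three components of a mixed ANOVA and does not make the three-level main effect the deciding test. In a pre/post design many readers would look to the interaction. That term is not diluted, and for Roland Morris it has 89% power at r = 0.5 and 99% at r = 0.7, above the 85% of the plain t test. This stands, and it limits the finding: the dilution affects the treatment term, not every test in the model. But the article does not name the interaction as decisive, and that term falls short at low correlations.

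Other points also stand in part:
- The correlation and the equal variances are assumed. If the baseline SD were 25% smaller, the main effect would have 85% at r = 0.3, though still 76% at r = 0.5.
- With no loss to follow-up, both terms exceed 80% for r from about 0.26 to 0.40. It is only at 28 per arm that no r gives both.
- Pain is largely unaffected if the effect is sustained.
- Chance imbalance is not bias. Both ANOVA terms keep their 5% error rate, so the loss is one of precision and of a result that moves with the baseline draw.

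The argument that this belongs in an analysis plan not shown does not carry. The article states the model, its terms and its time levels, so this is a choice it has made and not a detail it leaves open.

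**Conclusion.** The concern holds. The loss of one third in the treatment term is arithmetic. It requires only equal expected baselines and a full effect at both follow-ups, and it is larger if the effect fades. The power shortfall is conditional: it concerns disability, and with 28 analysed per arm it appears in the main effect once r exceeds about 0.26 and in the interaction when r is below about 0.37. Baseline-adjusted analysis at one follow-up has at least 85% power at any r, so it meets the stated 80% without knowledge of the correlation. The change should be made, but the planned tests are valid and the trial is not undermined without it.

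**What to change.** In the Statistical analysis section, take baseline out of the time factor. Analyse the 6-week and 3-month scores in a linear model for repeated measures, with group, visit and group-by-visit as terms and the baseline score as covariate. Name the baseline-adjusted between-arm difference, with its 95% CI, as the treatment effect for pain and for disability, in place of the three-level group main effect.

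State in advance whether that contrast is at one visit or is the mean of both. The mean is more powerful if the effect lasts, but if the Roland Morris effect is present only at 6 weeks its power is 52% to 71% for r = 0.3 to 0.7, against 88% to 99% for the 6-week contrast alone. In the Sample size calculation section, say that the 80% refers to the adjusted comparison.

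The cost is two or three sentences before data lock and one degree of freedom per outcome. No further patients, visits or data are needed, and the SPSS version already named can fit the model.

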### Procedures

We will recruit patients with chronic LBP (with symptoms of at least 3 months duration) who are seeking care for their problem. The reviews will take place in three stages: before treatment sessions begin, at the end of treatment (6 weeks) and 3 months after the end of the sessions. The envelopes will be opened sequentially by the treating physiotherapists, who will immediately provide the first session of treatment to the patients. Acupuncture points chosen will be selected based on the characteristics of patients and the relevant literature [11, 27].

The treatment protocol for the opening of the points will include the Daí Mai (VB41-TR5) meridian, points of local action and symptomatic points chosen by probing. The EG will be treated with electrical stimulation toning of 10 Hz for 10 minutes at the symptomatic points Zhenjin B23, Baihuanshu B30 and bilateral Mingmen VG4 (Table 1).

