#### Primary outcomes

##### Pain intensity

Pain intensity will be assessed using the numerical rating scale (NRS). The NRS is an 11-point scale ranging from 0 to 10 in which 0 indicates an absence of pain and 10 indicates unbearable pain. Participants will be asked to rate their average pain levels for the week prior to assessment [8].

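### The fallback for non-normal data, chosen by eye from histograms, is an independent-samples test that cannot replace the planned group-by-time or paired analyses

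*Protocol article*

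**What the plan says.** All the relevant text is in the Statistical analysis section of the protocol article.

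- Main analysis: "Repeated measures analysis of variance (ANOVA) will be used to investigate the effect of treatment (Acupuncture vs Electroacupuncture), time (baseline, post-treatment, 3 months follow up", together with "interaction terms between treatment group versus time".
- Within groups: "Two-sided paired t tests will use for within-group comparisons (comparing baseline to follow up".
- Check of the assumption: "Data normality will be tested through visual inspection of histograms".
- Fallback: "If we found non-normally distributed data, we will use the Kurtosis-Wallis test".

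The design to which these apply has two arms of 33 patients (Abstract, Methods/design). Each patient is assessed three times: "before treatment sessions begin, at the end of treatment (6 weeks) and 3 months after the end of the sessions" (Procedures). Both primary outcomes are bounded integer scores. For pain, "The NRS is an 11-point scale ranging from 0 to 10"; the Roland Morris score runs from 0 to 24.

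The section does not say which of the two analyses the fallback replaces, or whether it is applied to one visit, to change from baseline or to all visits. It also does not say what makes a histogram count as non-normal, or whether raw scores, changes or residuals are plotted.

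**The concern.** No test of the printed name is in use. The name is a slip for Kruskal-Wallis and matters little. What matters is the rule.

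First, the replacement does not fit what it replaces. Kruskal-Wallis assumes independent observations. The planned ANOVA asks whether the arms follow different courses over three visits, and the paired t tests use each patient as their own control. A test with no interaction term and no pairing does neither.

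Second, the choice of test, and with it the hypothesis tested, is made after the data are in, by eye. The ANOVA's normality assumption concerns residuals, so the shape of a raw-score histogram is a poor trigger. Scores that are bounded and integer-valued may look non-normal without harming the model. For pain, entry also requires a baseline score of at least 3, which cuts off the lower end.

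At stake is whether the between-group conclusion on the two primary outcomes comes from an analysis fixed in advance.

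**Working it through.** **Inputs.** Two arms, 33 per arm, three visits, 15% dropout, SD 1.9 (pain), difference 4 with SD 4.9 (Roland Morris), all from the protocol article. Completers per arm: 33 × 0.85 = 28.05, so 28. The article gives no within-patient correlation ρ; 0.3 to 0.7 is assumed. The article states no figure for the fallback, so there is none to reproduce. The planned sample size is not in dispute here.

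The article leaves the use of the test open, so each use is taken in turn. Nominal error is 5%, two-sided. Simulations used integer 0–10 scores with SD 1.9, at 28 and 33 per arm, with no difference between arms.

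**(a) One value per patient (one visit, or change from baseline).** With two groups Kruskal-Wallis is Mann-Whitney without continuity correction (p = 0.7132 from both in a check). Simulated error was 4.4 to 5.5%. This use is valid.

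**(b) In place of the within-group paired test.** The difference between two visit means has true variance proportional to 1 − ρ, but the test acts as if ρ were 0. To a large-sample approximation, the error is P(|Z| > 1.96/√(1 − ρ)).

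| ρ | 1.96/√(1 − ρ) | approximate error | simulated, 28 per arm |
|---|---|---|---|
| 0.3 | 1.96/0.837 = 2.34 | 1.9% | 2.1% |
| 0.5 | 1.96/0.707 = 2.77 | 0.6% | 1.1% |
| 0.7 | 1.96/0.548 = 3.58 | 0.03% | 0.1% |

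The test is far too conservative, so real within-group changes would be missed more often than necessary.

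**(c) Three visits stacked by group (hypothetical).** The variance of a group's mean over three visits is inflated by 1 + 2ρ. The approximate error is P(|Z| > 1.96/√(1 + 2ρ)).

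| ρ | 1.96/√(1 + 2ρ) | approximate error | simulated, 28 per arm |
|---|---|---|---|
| 0.3 | 1.96/1.265 = 1.55 | 12.1% | 11.2% |
| 0.5 | 1.96/1.414 = 1.39 | 16.6% | 16.7% |
| 0.7 | 1.96/1.549 = 1.27 | 20.6% | 20.5% |

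These figures assume no change over time. With an equal 1 SD improvement in both arms, the simulated error was 8.3 to 15.4%.

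**(d) Six group-by-time cells compared at once (hypothetical).** If both arms improve equally by 1 SD, the test rejects in about 100% of runs, because it picks up time and not treatment.

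**(e) Interaction.** Suppose the arms have equal average levels but cross between 6 weeks and follow-up (falls of 3 then 1 points against 1 then 3; ρ = 0.5, 28 per arm). Kruskal-Wallis on each patient's mean then rejects in 5.4% of runs, whereas a t test on the contrast between the two follow-up visits rejects in about 100%. A single rank test on patient averages does not see the interaction that the ANOVA was planned to test.

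**Power under use (a).** For Roland Morris, d = 4/4.9 = 0.82. At 28 per arm a t test at one visit has 85% power and Kruskal-Wallis about 83%, so the rank test itself costs about 2 points.

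**The case against.** The strongest reply is that the ordinary reading of a rank fallback in a two-arm trial is a comparison of the arms on one value per patient. Used so, the test holds its 5% level. On change scores it uses baseline, keeps one row per patient and tests a between-group difference in change, which for two visits is the group-by-time contrast. The misprint is trivial, and a condensed article may leave the tested variable to a fuller plan.

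Much of this stands. A reader might infer that the fallback will give a wrong p-value for the primary comparison. The article does not support that: it nowhere proposes stacking visits or comparing six cells, and the inflated errors belong only to those uses. A reader might also infer a serious loss of power. That does not follow either, since 83% remains above the planned 80%; a larger gap appears only against a baseline-adjusted analysis, which the article does not plan. Nor do the documents show that the fallback would be triggered, as they give no data on the distributions.

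What the reply does not remove is the rule itself. The article states a switch made by eye, and names an independent-samples test as the only alternative to both a three-visit interaction model and paired tests. That is a stated mismatch and not just detail left out. The benign use is one that a reader has to supply.

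**Conclusion.** The point holds in limited form. The article fixes a data-dependent switch, with no criterion, from a group-by-time model and paired t tests to a test without interaction or pairing. Kruskal-Wallis cannot take over the three-visit group-by-time test in one step. In place of the within-group tests its error falls to about 0 to 2% (assumed ρ from 0.7 down to 0.3). Errors of about 11 to 20% would arise only if visits were stacked with no time trend, a use the article does not state. On one visit or on change scores the test is sound, at a cost of about 2 points of power for Roland Morris. The main harm is that the primary test could be chosen after seeing the data. It affects both primary outcomes and is easily removed before analysis.

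**What to change.** Delete the switch. Name one primary between-group analysis that stands whatever the histograms show. This can be the planned repeated measures model with a stated group-by-time contrast or, better, a baseline-adjusted longitudinal model adopted in its place; the article does not contain the latter, so it would be a change of primary analysis and should be recorded as one. Check residuals and not raw histograms. As a sensitivity analysis only, report a rank test on change scores, or a bootstrap or permutation interval for the same between-group difference. If a within-group rank test is wanted, use the Wilcoxon signed-rank test.

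The cost is a few sentences in the analysis section and one short sensitivity analysis. No new data or patients are needed. Moving to a baseline-adjusted model would take somewhat more rewriting than deleting the switch alone.

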#### Ethics and data security

This trial was approved by the Ethics Committee of the School of Medicine of the University of Sao Paulo (protocol study 350/13). All patients will be asked to provide written, informed consent prior to randomization, using standard forms. Data access and storage will be in accordance with the National Health and Medical Research Council guidelines. This trial is registered on ClinicalTrials.gov (a service of the US National Institutes of Health) under the number NCT02039037 (October 30^th^, 2013).

## Discussion

The results of this study will contribute to a better understanding of the effectiveness of Electroacupunture and acupuncture in patients with chronic LBP in the short and medium term. The results of this study may help physical therapists and acupuncturists in their clinical decision making and to detect relevant clinical treatment with a low risk of bias. To increase the clinical relevance of the test results.

This trial was designed to reproduce the intervention exactly as it is currently recommended by TCM as well as guidelines [1, 10, 30] on the treatment of patients with chronic LBP, and we hope that this study will help to reduce pain and disability. Studies have already shown the effectiveness of acupuncture as an intervention in patients with LBP compared with placebo-controlled groups [2, 4, 9, 28]: in our study both techniques are applied separately, thus we can evaluate the effects separately; this has not been previously reported, and there are currently no studies demonstrating whether one technique is more effective than the other. There is currently no answer to the question: “Is electroacupuncture better than manual acupuncture?” There is a tendency, among modern acupuncturists, to consider this a truism, but there is no scientific evidence to back up this statement. More research is necessary, specifically designed to respond that question.

The study will contribute to clinical practice by providing evidence that will help guide decisions about the appropriate treatment of patients with chronic LBP and also may contribute a solution to the difficult problem of the chronicity of acute pain, and promote the clinical application of EA our acupuncture analgesia. The results will be published once the study is completed.

